## Materials and methods

### Study design

The PAINLESS study, funded by Horizon Europe (call HORIZON-HLTH-2021-DISEASE-04; Project ID: 101047367), is an international multicenter, randomized, placebo-controlled, triple-blind, three-armed clinical trial to test the efficacy of 15 sessions of home-based tES in patients with chronic cancer-related pain. We will explore the effects of anodal tDCS of the left M1 and 10 Hz tACS over the DLPFC on clinical pain, quality of life, cognitive and emotional functioning, fatigue, sleep quality, as well as psychophysical and neurophysiological markers of central pain processing using QST and EEG respectively. Measurement visits will take place at baseline (T0), post-tES intervention (T1), and three months (T2) following the intervention. At the last visit, six months (T3) following the intervention, only the NRS of intensity, unpleasantness and interference of cancer pain with daily life, as well as the NRS of fatigue and sleep quality, will be assessed.

A randomization list is created for an independent researcher for all the clinical sites involved. The study flowchart is described below and summarized in Table 1.

**Table 1 Tab1:** Study protocol

		Base line	15-days tES intervention		Follow up		
Study activities	Screening Visit 1	Visit 2 (T0)	Visit 3 (Session 1)	Sessions 2–15	Visit 4 (T1)	3-months follow up Visit 5 (T2)	6-months follow up Visit 6 (T3)
Location of meeting	Home or Clinic	Clinic	Clinic	Home	Clinic	Clinic	Home
Screening	✔						
Informed consent and anamnesis	✔						
Baseline questionnaires		✔					
Clinical Interview and History	✔	✔			✔		
NRS pain assessment		Pain intensity rated daily on NRS including 15 days baseline recording				✔	✔
tES training for home stimulation			✔				
Battery of questionnaires		✔			✔	✔	✔
QST-EEG		✔			✔	✔	
Medication diary			✔	✔	✔	✔	
Side/adverse effects questionnaire			✔	✔	✔		
Home-based feasibility questionnaire					✔		
Blinding and satisfactory questions					✔	✔	✔

*tES* transcranial electrical stimulation, *NRS* numerical rating scale, *QST* quantitative sensory testing, *EEG* electroencephalography.

#### Visit 1: screening visit (Study site)

In an interview conducted by the study clinician and a co-investigator responsible for the study, the medical and social background of the participant will be explored with an emphasis on any apparent exclusion criteria. A brief medical screening will be conducted based on the medical history of the patient. During the conversation, patients will be informed about the objective and purpose of the study, including any potential risks of the investigation. The consent form for participation in the study will be signed after the participants and the study clinician are certain of having made an informed decision and having obtained a full case history. During informed consent, the patients’ authorization to access data from their previous clinic records will be requested. It is also an option for each participant to involve a caregiver of theirs, who will help to conduct the home-based tES sessions and provide answers to some questionnaires. The caregivers will also have to sign the informed consent.

#### Visit 2. Baseline assessment (Study site; T0)

During the interview, sociodemographic (e.g., sex, age, lifestyle, medication pattern) and clinical data (comorbidities, type of cancer, extension, time since diagnosis, evolution, previous chronic diseases, risk factors for cancer, antecedents of cancer) will be collected.Patients will also fill in a battery of questionnaires on the web-based online PAINLESS platform (refer to Sect. 5.1 for further details) to assess pain and related symptoms (sleep quality, quality of life, fatigue…) and will take part in the QST and EEG measures. To avoid long assessment periods at the study site, participants will be offered the option to be interviewed online, via a secured videoconference platform and to fill in the questionnaires from home. Moreover, the relatives or caregivers will complete questionnaires addressing their quality of life, the burden of caring for the patients, and their socio-economic backgrounds. Following Visit 2, the patients will be randomly allocated to one of the three intervention groups, using the previously created randomization list. Both patients and clinicians/researchers responsible for the delivery of tES will be blinded to the treatment condition.

#### Visit 3. First tES session and training (Study site)

The first stimulation session will take place in the clinic, supervised by the investigator or clinical staff at the study site. This session also aims to train the patient and/or caregiver to operate and use the tES setup. Participants will receive the tES kit for home use. Further details on the training are found in Sect. 3. Before starting the tES intervention, the patients will complete the daily NRS addressing core symptoms and note medication intake and dosage in a medication diary during 15 days prior to the stimulation session. In addition, during the 15-day period prior to neurostimulation, patients will respond to two questionnaires created ad-hoc for this project, one to assess cognitive complaints and the other to assess socio-economic variables (medical and non-medical) related to the cancer care. The questionnaires will be filled in on the PAINLESS platform.

#### Sessions 2–15. tES intervention (Home-based).

Participants will conduct the tES at home and will complete the assessment questionnaires daily, in the same way as in the pre-treatment baseline period. Besides, during the intervention, participants will report the occurrence of any side or adverse effects of the stimulation.

#### Visit 4. Post-treatment assessment (Study site; T1).

The investigator will interview the patients to assess medication intake, receipt of any non-pharmacological treatment, and number of hours slept in the 24 h prior to the visit. The battery of questionnaires for patients and caregivers as well as the QST and EEG measures for the patients will be conducted, as in Visit 2. Again, the patients will be asked to fill in NRS of the primary and secondary endpoints during 15 days after the treatment. Patients will also fill in the questionnaire on cognitive complaints as in the pre-treatment and report global ratings of improvement and satisfaction with the home-based tES intervention.

#### Visit 5. Three-month follow-up (Study site; T2)

The same procedure as in Visit 4, including QST and EEG assessments will be conducted three-months following the tES intervention. Caregivers will fill in their respective set of questionnaires. The socio-economic questionnaire will also be administered to both patients and relatives/caregivers. Again, we will ask the participants to fill in NRS of the primary and secondary endpoints during 15 days in this follow-up period.

#### Visit 6. Six-month follow-up (Telephone or online; T3)

Six months after the tES intervention, investigators will call the patients via telephone or online to measure the core clinical outcomes on an NRS scale with a one-week recall period. No QST or EEG will be performed. Caregivers will fill in their respective set of questionnaires. The socio-economic questionnaire and a satisfaction survey will also be administered to both patients and relatives/caregivers.

### Specific aims and hypotheses

This multicenter study will address many aspects of cancer-related persistent pain including its potential treatment with repeated tES and assessment of the effectiveness of the therapy using self-reported assessment of different symptoms of the disease, psychophysical testing using QST and neurophysiological testing using EEG. The aims and hypotheses of the study are as follows:Aim 1: To determine the therapeutic effects of 15-day home-based anodal tDCS and tACS interventions (compared to sham stimulation) on pain intensity (primary outcome), other dimensions of pain (pain unpleasantness, catastrophizing, interference), quality of life, cancer-associated symptoms (fatigue, depression, anxiety, sleep fragmentation, cognitive impairment), and global functioning among patients with cancer-related persistent pain. We hypothesize that compared to sham, tDCS and tACS will reduce clinical pain and associated symptoms as well as improve quality of life and global functioning. We expect that anodal tDCS might have a stronger effect on pain intensity, while tACS can have a stronger effect of decreasing stress, emotional processing of pain and improving quality of life. We will also test the feasibility of the home-administered tES (analyzing dropout rates, satisfaction scores, adverse and side-effects…). The potential long-term benefits of the interventions will also be addressed at three and six months post-treatment follow-ups.Aim 2: To identify psychophysical and neurophysiological predictors and mediators of tES-induced analgesia in patients with cancer pain. We hypothesize that the improvement in clinical pain will be mediated by intervention-induced adaptive changes in (i) nociceptive and pain modulatory system using QST indices and through contact heat-evoked potentials (CHEPs) using concurrent heat painful stimuli and EEG, as well as (ii) in oscillatory activity measured by resting state EEG.Aim 3: To identify responders to the tES interventions based on clinically relevant reduction in pain intensity (≥ 30%) and to characterize them according to central pain biomarkers using QST, EEG measures and/or sociodemographic, climical and disease related data. We hypothesize that indices of pain modulation and perception will be sensitive to predict treatment outcomes.

### Study sites and coordination across sites

This clinical study will be conducted at seven study sites, comprising of research centers and hospitals, located in five countries. The study sites are the Servizo Galego de Saúde – Fundación Instituto de Investigación Sanitaria de Santiago de Compostela (SERGAS-FIDIS), Servizo Galego de Saúde - Fundación Pública Galega de Investigación Biomédica Galicia Sur (SERGAS-FBGS), and Universidade de Santiago de Compostela (USC) located in Spain; the Israel Institute of Technology (TECHNION) in Israel; the Universitätsmedizin Göttingen (UMG) in Germany; and the Ente Ospedaliero Cantonale (EOC) in Switzerland. The centers have been selected based on their expertise in either chronic pain, cancer, QST, EEG, and/or neuromodulation. The trial is registered at the German Clinical Trial Register (www.drks.de; ID: DRKS00031070). A lead study coordinator responsible for the administration of the protocol will be assigned at each study site. All the study sites will use identical study methods as described in the protocol, as the staff involved has been trained in on-site and online sessions. The questionnaires and instructions to patients will be provided in the local language of the patients depending on their nationality (Spain- Spanish; Germany- German; Israel- Hebrew; Switzerland- Italian).

The study will be led by the UMG team and the final analysis will be conducted by the USC. The study will use a centralized data management system and a centralized document library (PAINLESS platform; refer to Sect. 5.1. for further details). The PAINLESS consortium hosts monthly videoconferences attended by the study personnel to promote consistent and open communication within the consortium. These meetings are included to ensure consistency among study sites and timely discuss questions or concerns arising during the study course.

### Participants

The PAINLESS study aims to include 450 patients with cancer pain. A relative or caregiver of each patient will participate in the assessments. Each study site will recruit the following number of participants: SERGAS-FIDIS (*n* = 70), SERGAS-FBGS (*n* = 70), USC (*n* = 90), TECHNION (*n* = 100), UMG (*n* = 90), and EOC (*n* = 50) to meet the goal of 450 participants. The underperformance of individual clinical sites in recruitment will be equally distributed by the remaining participating centers until the estimated number of participants is reached. Recruitment will be performed over two years in the involved centers and there will be no competition between the clinical sites.

Each study site will follow a multimodal recruitment strategy involving both clinic-based and community-based methods, tailored to meet the recruitment needs of each study site. Participants will be ambulatory patients receiving care in oncology services, pain units of hospitals, or palliative care services in the respective country. Advertisements through recruitment flyers, letters, information talks for patients, and newspaper articles will be made in hospitals, local oncological practices, and self-help groups for cancer patients. In case the desired number of participants is not reached through these channels for each study site, national associations of cancer patients may be contacted to increase enrolment. Efforts will be titrated to maintain a consistent flow of participants and avoid long waiting times.

Upon interest in participation, the patient will first contact the local study team by e-mail or telephone call. A short pre-screening phone call will be done to inform the patients about the general aspects of the study (duration, place, frequency of visits, commitments), and an appointment will be scheduled for the first visit. At the first visit, the medical doctor or researcher will review the clinical history of the patients to select those that fulfil the inclusion criteria.

We designed the inclusion and exclusion criteria of the study to facilitate the enrolment of a representative sample of cancer patients with chronic pain, whilst optimizing the validity of our study findings and participant safety. Only participants who fulfill all the inclusion criteria and do not meet any of the exclusion criteria will be included in the study. Participants are allowed to continue their treatment-as-usual routine, including medication and non-pharmacological therapies.

Inclusion criteria:

Diagnosis of cancer affecting the lung, breast, pancreas, or colon (with/-out metastases, except for metastases in the central nervous system).Patients aged ≥ 18 years and ≤ 75 years.Cancer-related pain must be present for over 1 month prior to enrolment, with a pain intensity rated ≥ 5 on a 0–10 Numeric Rating Scale (NRS).Ability to provide informed consent.Ability to self-report pain.Life expectancy of ≥ 6 months.Ability to use the Internet and WhatsApp (Meta, California, USA, etc.) or have a person (relative or caregiver) to support them.

Exclusion criteria:

Pregnant women or women of fertile age who did not have efficacious contraception during the whole period of the study.45 kg < Body weight < 120 kg.Neurological or psychiatric diseases including epilepsy (except anxiety or depression).Unstable medical conditions (e.g., uncontrolled diabetes, uncompensated cardiac issues, heart failure, or chronic obstructive pulmonary disease).History of neurosurgery, traumatic brain injury with loss of consciousness, and/or cortical lesion. History of unexplained or repeated loss of consciousness.History of non-malignant chronic pain.Presence of implanted metallic devices in head, neck or chest, as this is a contraindication for tES.

Caregivers of patients should be consenting adults ≥ 18 years old cohabiting with the participants and able to navigate the Internet and WhatsApp.

Participants may decline to participate at any study phase, without suffering any negative consequence. They will be asked to state their reasons for dropping out for monitoring purposes.

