## Data management and analysis

### Online data management system

The clinical data of the patients will be collected in the web-based PAINLESS platform, which was developed by Software Imaging & Vision information technology company (SIMAVI, Bucharest, Romania). The PAINLESS system is maintained on the infrastructure of the Supercomputing Centre of Galicia along with the associated collected data.

Patient data will be treated as strictly confidential, and the data collection will be pseudo-anonymized, protecting the participants’ identity. For this purpose, the study doctor will assign a unique code called the “Painless ID” to the participant with which they will be identified during all subsequent phases of the study. The data relevant to the study, except for patients’ names, will be recorded, processed, and stored together with this unique code identifier and all the clinical data related to the state of health. The profile data of the patient is stored in a different repository to the clinical data in order to create another layer of security. Only the physician and authorized parties will be able to link this code to the patients’ real identity. The only stored personal data relevant to the study are age and sex and does not identify the patient.

The system automatizes a lot of the processes related to the study. The registration process is automatized through the PAINLESS Platform. There is an Eligibility Questionnaire where the clinician enters the Painless ID and the answers the patient gave to some questions that are important to determine if the patient is eligible to participate in the project. The system then compares the answers to the eligibility criteria determined by the consortium and returns an Eligibility Code only if the patient is declared eligible. The patient can then use the Eligibility Code to register through the platform and will receive an email that they have successfully registered to the Painless Platform. A similar process is performed for caregivers, a caregiver code is generated associated with an existing patient and can be used code to register in the platform. Password recovery can also be done through email. The registration process has multiple steps in order to ensure the Painless Platform is a closed ecosystem and only selected personnel and patients have access for security purposes.

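### The body-weight range stands in the exclusion list, so read literally it bars everyone strictly between 45 and 120 kg

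*Protocol article*

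**What the plan says.** All eligibility rules are in the Participants section of the protocol article.

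- The second item under the exclusion criteria is "45 kg < Body weight < 120 kg".
- The rule for applying the lists is explicit: "Only participants who fulfill all the inclusion criteria and do not meet any of the exclusion criteria will be included in the study".
- The purpose of the criteria is given as "to facilitate the enrolment of a representative sample of cancer patients with chronic pain", alongside validity of the findings and participant safety.
- The recruitment goal is also stated: "The PAINLESS study aims to include 450 patients with cancer pain".

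The inclusion list has no weight item, and no other part of the article gives a weight limit.

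The section on the online data management system describes an automated step in registration. The clinician enters the patient's answers to certain eligibility questions. "The system then compares the answers to the eligibility criteria determined by the consortium", and a registration code is issued only to patients found eligible.

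**The concern.** The other items in the exclusion list describe conditions that keep a patient out. A bounded middle range in that list does the same: being inside it disqualifies the patient. Limits of this form normally mark off the extremes, so the printed line appears to say the opposite of what was meant.

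Eligibility criteria define the trial population. If the line were followed as printed, the trial would admit on weight only the two tails. If staff silently correct it, the patients they enrol between the limits are ineligible under the published text, and the corrected rule is written down nowhere in the article. Either way, a reader cannot tell from the article which population is being studied with respect to weight.

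**Working it through.** No figure in the article has to be reproduced here. The check is one of logic.

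**Inputs** (all from the Participants section)

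- Exclusion condition E: 45 < w < 120, where w is body weight in kg.
- Application rule: meeting any one exclusion criterion bars entry.
- No weight condition in the inclusion list.

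**Step 1: who passes on weight.** A patient passes only if E is false. The negation of (w > 45 and w < 120) is (w ≤ 45 or w ≥ 120).

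| Weight (kg) | Is E met? | Result on weight |
|---|---|---|
| 40 | no | admitted |
| 45 | no | admitted |
| 46 | yes | excluded |
| 70 | yes | excluded |
| 119 | yes | excluded |
| 120 | no | admitted |
| 130 | no | admitted |

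Both inequalities are strict, so patients at exactly 45 kg or 120 kg are admitted too.

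**Step 2: compare with the stated aims.** The same section wants a representative sample and 450 patients. The article gives no weight distribution. On the ordinary assumption that most adults weigh between 45 and 120 kg, a rule that admits only the tails cannot deliver either.

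**Step 3: can the intended rule be recovered from the text?** Its direction can be guessed, but its exact form cannot.

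| Possible rewording | 45 kg exactly | 120 kg exactly | Between the limits | Beyond the limits |
|---|---|---|---|---|
| Printed range moved unchanged to the inclusion list | not admitted | not admitted | admitted | not admitted |
| Exclude if w < 45 or w > 120 | admitted | admitted | admitted | not admitted |
| Both signs reversed in one chain, 45 > w > 120, kept as an exclusion | admitted | admitted | admitted | admitted |

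The first two rows differ only at the boundary values. The third requires a weight below 45 kg and above 120 kg at once. No patient can meet that, so it would exclude nobody and is not a repair. The rows show the logic only; they do not say which limits are right.

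**The case against.** The strongest reply is that this is an obvious slip in a journal article that condenses a fuller protocol not shown here. A medical doctor or researcher reviews each patient's history at the first visit, staff are trained, and the consortium meets monthly to keep the sites consistent. A rule that turned away nearly every candidate would be noticed at once. The line also does not touch randomisation, the sample size or the analysis.

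Much of this stands. It is a wording error, not a deliberate design choice, and harm in practice may be nil. It does not remove the point, because the article does not leave the criterion to another document. It states it, completely and legibly, in the wrong direction, and nothing elsewhere corrects it.

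Stronger readings are tempting and are not supported:

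- A reader might infer that the platform automatically rejects patients between 45 and 120 kg. The article says only that certain questions are checked. It does not say that weight is among them or how it is coded.
- A reader might infer that sites working in different languages apply different versions. The local-language provision concerns questionnaires and patient instructions, not eligibility criteria.
- A reader might infer that nearly all of the 450 intended patients are being lost, or that centres are enrolling different populations. The first is what literal application would imply under ordinary adult weights. The second is conjecture. The article reports neither.

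**Conclusion.** The point holds as an error in an operative eligibility rule. Followed exactly, the criterion excludes every patient strictly between 45 and 120 kg and admits on weight only those at or beyond the limits. That contradicts the section's own aim and cannot sensibly support a 450-patient trial.

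The logical result needs no assumption. The statement that the rule would exclude most candidates rests on ordinary adult weights, because the article gives no distribution; no percentage can be put on it from the text. That the line is a drafting slip is probable, not shown. What the sites and the platform actually apply cannot be seen from the article.

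**What to change.** 1. Reconcile the direction of the criterion with its placement. Either state the range as an inclusion criterion, or keep it as an exclusion written as two separate conditions joined by *or*. Do not simply reverse both signs in the single chain.
2. Have the clinical lead confirm the limits and state explicitly whether the two boundary values are included.
3. Check whether the platform's eligibility questionnaire asks for weight and, if so, how the rule is coded.
4. If it was coded as printed, re-check the eligibility of anyone already screened.

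The cost is a one-line correction and a check of the eligibility form. Re-checking screened patients is needed only if step 3 finds the printed rule in the code.
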